### Maternal assessments

Well-baby clinics provide mothers with a Road-to-Health card that is taken to each healthcare visit and includes information about immunizations and basic health data. All mothers are entitled to ZAR300 monthly as a child grant and the majority of mothers obtain this grant by 24 months after birth in the Eastern Cape [38, 39].

#### General health

Maternal adherence to medical regimens in pregnancy will be monitored, as well as HIV testing in pregnancy, receiving the results at a clinic visit at 1 week post birth, and prenatal vitamins. Adherence of the mother to prescribed healthcare and health routines for herself, her baby, and her partners will be assessed. Alcohol and substance use will be monitored over time, including any alcohol use in pregnancy, frequency of use, the number of drinks per use, and withdrawal symptoms using the three-item AUDIT-C [40, 41], a standardized measure with scores > 2 indicating problematic drinking; scored as 1 if absent, 0 if present.

#### Mental health

The Edinburgh Perinatal Depression Inventory [42], a 10-item scale, will yield the primary depression score and classification as depressed if the score is over 13. Additional maternal health measures are included, but since they are not part of the primary outcome, are not listed here.

#### HIV-related tasks for MLH

MLH have six tasks to accomplish during pregnancy and additional tasks for the first 6 months post-birth related to their children, which will be rated 0 (non-occurring) or 1 (occurring) for each task. These tasks are to take highly active antiretroviral therapy (ARV) from the moment they are diagnosed with HIV irrespective of CD4 count (and continuing for life as per the SA guidelines); have at least one viral load (VL) tested during pregnancy which is less than 400 copies/ mL and have VL taken at least monthly until the cessation of breastfeeding; give child Nevirapine syrup for 6 weeks post-birth (or Nevirapine and AZT syrup for 12 weeks if deemed high risk by a clinician); get child HIV tested with PCR at birth and at 10 -14 weeks post delivery; and, breastfeed exclusively for 6 months. MLH will also report to who, when, and how their HIV status was disclosed. ARV adherence, and their child’s ARV adherence until receipt of their HIV test results, method of feeding, and whether only breastfeeding for 6 months occured will also be recorded. Information on MLHs’ strategy to protect their partner will be collected. MLH must continue HIV care post delivery at their hospital or local clinic following childbirth, have their VL, creatinine, and CD4 monitored, and take ARV consistently.

### Child measures

#### General health

Children’s physical growth is reflected in their age-standardized weight, height, weight-for-height, and head circumference based on the World Health Organization’s (WHO) age-adjusted norms (http://www.who.int/childgrowth/standards/en/) [43]. We will use the child’s government-issued Road-to-Health card and hospitalizations at each assessment point. Well-baby clinic visits should include a critical visit at the 1-week post-birth follow-up.

#### Immunizations

Recommended visits on baby’s health card with immunizations for diphtheria, tetanus, pertusis, HIV, polio, measles, and hepatitis B prior to 24 months will be recorded.

#### Development

The WHO developmental milestones for children at 12 (four tasks) and 24 months (six tasks) and the motor and speech developmental milestones will be administered at 12 months (four tasks) and 24 months (six tasks) [44]. The Bayley Scales of Infant and Toddler Development, Third Edition will be used to assess the developmental outcome of the children at 24 months corrected for age (for prematurity) [45]. The child is tested on three major aspects of development, namely cognition, language, and motor development. The scale has good test-retest reliability and concurrent validity when compared to other infant tests among South African children [46] and with HIV-positive babies on ARV. At 24 months, we will also monitor the children’s behavioral and emotional problems using the Child Behavior Checklist [47–49]. Additional child measures are included, but since they are not part of the primary outcome, are not listed here.

### Intervention

#### SC

All CHWs will receive a mobile phone and initial Philani training for conducting home visits. The CHW will visit the mothers twice monthly during pregnancy until children are 6 months and then monthly until the children reach 2 years of age. All mothers are asked to re-enroll annually with voluntary informed consent at each assessment. The initial messages to CHWs with pregnancy and new mothers and the first 6 months of life are (1) HIV testing, adherence to therapy for MLH, nevirapine at childbirth, hospital delivery, a single feeding method for 6 months, PCR infant HIV testing at 6 weeks, and MLH reengagement in care and adherence to medication; (2) breastfeeding solely for 6 months, monitored by charting growth at each visit, and problem solving on how and where to get food; (3) reducing and eliminating alcohol use; (4) getting the child grant; (5) engaging in pleasant activities and building a social network; and (6) attending clinic visits (four antenatal visits, Well-Child visits, immunizations). After the first 6 months, the CHW focuses on encouraging mothers to stimulate and support their children daily.

Households in the target areas will be visited by government-funded CHWs. This is currently the SC in the Eastern Cape in the wards adjacent to the Zithulele catchment area (although not in all of the Eastern Cape). The existing government-implemented training, monitoring, and supervision structures will remain in place with the only addition being an initial Philani training for conducting home visits. The geographic areas covered by each of the existing CHWs in two wards will be defined and all pregnant women coming to the clinics will be recruited with voluntary informed consent by paraprofessionals or the assessment team. CHWs in the SC will refer all mothers to local clinics for HIV, blood sugar, and pregnancy testing. The rates of visits and tests are available from clinic data and also will be individually collected by the assessment team.

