### Setting

The OR Tambo District is a rural, hilly area in the Eastern Cape of South Africa accessible on a 150 km paved road east from Umtata and north of East London, with very high unemployment. The area is ancient tribal land, with the tribe allowing only minimal industrialization. Zithulele Hospital serves 130,000 families with nine local clinics. To reach clinics, a patient must cover large distances of hilly terrain either by walking or using the expensive and infrequent mini bus taxis. Aerial maps provided information on the density of each potential study area.

With the support of the District Health Officer, the team has documented the catchment areas of each CHW assigned to eight clinics in the catchment area of Zithulele Hospital. Data on access to electricity (8% in the region), water tanks (16%), flush toilets (few), distance from the road and the local clinics, and hilliness was used to identify areas of about 200 households each. The areas were matched by UCLA and all CHWs at each clinic (3–5 per clinic) were randomized to either (1) the Accountable Care (AC) condition, in which the PIM supervision and training models will be implemented (4 clinics, 16 CHW, 450 households); or (2) Standard Care (SC) by existing government supervisors and CHWs implementing home visits (4 clinics, 21 CHW, 450 households). Risk of contamination is very low given it is a deeply rural region with vast distances between villages and even homes. Figure 2 outlines the design of the randomized controlled trial (RCT), with the planned follow-up assessments by an independent team of assessors.

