### Recruitment

Female research interviewers have been placed in each clinic to recruit all pregnant women and securing voluntary informed consent. Each recruiter covers one clinic in the AC and one clinic in the SC condition. The eligibility criteria to participate in the study will be living in the catchment area and not identified as psychotic or delusional based on the interviewer’s judgment. Exclusion criteria are inability to give informed consent, inability to converse with the interviewer or the CHW, and death of the mother or infant. After consent, an independent team of assessors will conduct the follow-up assessments at the mother’s home.

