There will be a “flag system” to prompt the CHW and supervisor when visits are due by the CHW and when a follow-up is needed. In addition to gathering real-time data on the health of the household, the mobile phone monitoring system automatically lists all follow-up visits needed for each week. For example, the CHW is expected to reach all households in their catchment area within a maximum of a 6-month period. Pregnant mothers are to be visited monthly and every 2 weeks within the last 6 weeks of pregnancy. A household with a severely malnourished or stunted child must be visited weekly. A household with a child within one SD of the normal height and weight only needs to be visited monthly. MLHs must be visited more often both in pregnancy and post-birth, especially if there has been no reengagement in care following childbirth (See Table 2).

**Table 2 Tab2:** Identification of responsibility for administrative and implementation functions with community health workers (CHWs)

	Standard Care	Accountable Care
Hiring	Local government	Local government
Salary	Local government	Local government
Training	Initial Philani Intervention Model (PIM) training	Initial PIM training and mobile phones provided
Visit documentation	Log sheet	CHW will log home visits in real time on mobile phones and enter information about the pregnant women in a folder for follow up purposes
Supervision	Local government	PIM
Type of supervision	Log sheet	Random supervision visits every 2 weeks including real-time and data-informed feedback; support and reminders will be sent to CHW and supervisors via mobile phones (“flag system”)

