### Data analysis

A composite score will be calculated based on measures from birth to 24 months post-birth, similar to our composite measure in our previous RCT in Cape Town [33, 34]. It will be a sum of assessments of the attainment (1) or not (0) of well-being from 10 indicators of MCH. Outcomes will be assessed as present (1) or absent (0). Base rates influence the number of significant outcomes needed on individual domains to yield a significant result. To examine overall differences between MCH outcomes in the SC in contrast to the AC, a single index summing the 10 indicators will be calculated as the sum of 1 s, reflecting a score above the median (e.g., on months of breastfeeding) or present (getting all immunizations, attending > 3 antenatal visits), or 0 s, reflecting a score below the median or not present (e.g., no child grant, no maternal HIV testing in pregnancy).

The primary analyses will examine cumulative change across multiple indicators of maternal and infant health. For outcomes only assessed at 24 months, differences between AC and SC conditions will be examined using random effects regression models to control for neighborhood clustering. Differences between outcomes assessed at baseline, 6, 15, and 24 months will be explored using multi-level models adjusting for repeated measures and neighborhood effects. Data analysis will be conducted using SAS software version 9.2 [50]. Linear regression will be used for continuous variables, and logistic regression and Poisson/negative binomial regression will be implemented for binary and count outcomes, respectively. Logistic regression will be used for longitudinal binary outcomes.

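### Women are enrolled after allocation and only when they come to a clinic, so who is enrolled, and how early in pregnancy, can differ by arm; the likely shift is modest and mainly toward no effect.

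*Protocol article*

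**What the plan says.** The Setting section reports in the past tense that the CHWs at each clinic "were randomized to either (1) the Accountable Care (AC) condition" or to SC. Trial status says that recruitment was still to start when the article was submitted. Women therefore enter clusters whose arm is already fixed.

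Entry is through the clinic. Under Recruitment: "Female research interviewers have been placed in each clinic to recruit all pregnant women". Under Intervention, SC: "all pregnant women coming to the clinics will be recruited with voluntary informed consent". The second sentence stands under the SC heading, but the first covers every clinic. No household or community route is described. On who qualifies, Recruitment says "The eligibility criteria to participate in the study will be living in the catchment area", and gives no gestational-age window.

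Attendance is something the programme teaches. The CHW messages include "attending clinic visits (four antenatal visits, Well-Child visits, immunizations". They belong to the initial training that both arms receive, and SC CHWs are also to refer mothers to clinics for testing. In AC, supervisors accompany CHWs and review their data, and a flag system lists visits that are due, under which "the CHW is expected to reach all households in their catchment area within a maximum of a 6-month period".

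Antenatal attendance is also outcome content. Data analysis gives, as an example of a scored item, "present (getting all immunizations, attending > 3 antenatal visits"; HIV testing in pregnancy is another.

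**The concern.** Randomising clinics balances the women who live in the areas. It does not balance the women who choose to attend after the arms have begun to differ. CHWs visit households, not only enrolled women, so AC can act on a woman before she is recruited. If better-supervised CHWs bring in some women who would otherwise not have come, or would have come too late to be recruited, the AC sample contains a group with no counterpart in the SC sample. The Setting section makes non-attendance plausible: it describes long distances over hills and scarce, costly transport.

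At stake is the primary comparison of the composite score. If the extra AC women are harder to reach and score lower, a real benefit is diluted. The adjustments that the article describes, for clustering and repeated measures, do not deal with selection into the sample. With a planned effect of only 0.21 SD, a small shift in composition is not negligible.

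**Working it through.** **Yardstick.** The plan gives no figure for this point. Its 0.21 SD (Power calculations) serves only as a scale. It is reproduced by 360 women per arm (80% of 450), two-sided alpha 0.05, power 0.80 and no clustering allowance: (1.960 + 0.842) x sqrt(2/360) = 0.209. How clustering entered that figure is a separate matter.

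**Can the sample depend on arm?** Four facts, read together:
1. Allocation comes before enrolment (Setting; Trial status).
2. Entry requires coming to a clinic (Recruitment; Intervention, SC).
3. Coming to a clinic is a taught behaviour in both arms, and AC adds means intended to improve delivery (Intervention, SC and AC).
4. No stated safeguard makes the set of attenders independent of arm. That "Each recruiter covers one clinic in the AC and one clinic in the SC condition" guards against differences between recruiters. Independent assessors guard against measurement bias. Distance between villages limits contamination.

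So the sample can depend on arm. The documents do not show that it will.

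**How large?** Let s be the share of the AC sample who attend only because of AC, D their deficit in indicators (out of 10), and SD the standard deviation of the composite. Assume that women who would attend anyway are alike in both arms. Then:

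shift in AC mean = -s x D / SD

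The documents give none of these inputs; all are assumptions.

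| s | D | SD | Shift (SD units) | Share of 0.21 |
|---|---|---|---|---|
| 0.03 | 1 | 2.0 | -0.015 | 7% |
| 0.05 | 1.5 | 1.75 | -0.043 | 20% |
| 0.10 | 2 | 1.5 | -0.133 | 63% |

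The middle row takes the midpoints of D and SD. The last row sets all three inputs at their unfavourable ends.

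**Cross-check from attendance rates.** If shares a0 (SC) and a1 (AC) of pregnant women reach a clinic, then s = (a1 - a0)/a1, and the size of the shift is d x (a1 - a0)/a1, with d the deficit in SD units (assumed 0.25 to 0.75).

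| a0 | a1 | s | Size of shift (SD) | Share of 0.21 |
|---|---|---|---|---|
| 0.90 | 0.95 | 0.053 | 0.013 to 0.039 | 6% to 19% |
| 0.80 | 0.90 | 0.111 | 0.028 to 0.083 | 13% to 40% |
| 0.70 | 0.90 | 0.222 | 0.056 to 0.167 | 26% to 79% |
| equal | equal | 0 | 0 | 0% |

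The middle row of the first table implies d = 1.5/1.75 = 0.86, a little above this range, so it is not a mild choice. A shift of 0.04 SD is near the top of what a gap of five percentage points gives here.

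**The case against.** The case against has several parts, and much of it stands.

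- **The push to clinics exists in both arms.** The message comes from shared training, and SC CHWs refer mothers to clinics. The outcomes that the article names as reported by AC CHWs do not include antenatal attendance. This stands: any difference can come only from AC's added supervision and flags. But the effect of that addition is what the trial sets out to test, so it cannot be assumed to be nil.
- **Entry and outcome are different thresholds.** Entry takes one visit; the index example needs more than three. Moving a woman from two visits to four does not change who is enrolled. This stands: composition changes only through women who would otherwise not attend, or would attend too late to be recruited.
- **Earlier attendance by the same women.** A reader might infer a bias in favour of AC because earlier entry leaves more time to exceed three visits. The documents do not support that. If the women are the same, more visits are a real effect of the intervention. It would be an artefact only if visits were counted from enrolment. Nothing says that they are, and assessors are to use health case files.
- **Never-attenders.** A reader might infer that leaving them out biases the comparison. They are absent from both arms, so this alone limits only the population to which the result applies.
- **A condensed article.** Enrolment items, recruitment tables and sensitivity analyses may sit in a fuller protocol or analysis plan, and their absence here is no fault. Entry through the clinic after allocation, however, is a choice that this article states.

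**Conclusion.** The concern holds in a limited form. Enrolment follows allocation and runs only through the clinics, and AC is intended to strengthen work that includes urging clinic attendance. The mix of women enrolled and their gestation at entry can therefore differ by arm, and nothing in the stated design prevents it.

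The size is unknown. It is zero if attendance is equal. With 5% extra attenders, a deficit of 1.5 indicators and an SD of 1.75, it is about -0.04 SD, or 20% of the planned effect. The direction is mainly toward no effect, given the assumption that the extra women score lower. A reader might arrive at about a third of the planned effect (0.05 x 2 / 1.5 = 0.067 SD, 32% of 0.21), but that pairs the largest deficit with the smallest SD and is not a central value.

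**What to change.** Keep clinic recruitment and make four changes.

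1. Approach women at their first antenatal visit in both arms. Record gestational age and any CHW contact already made in this pregnancy, and report both by arm.
2. Count antenatal visits and HIV testing over the whole pregnancy from clinic records, not from the date of enrolment. Earlier entry then cannot by itself raise the score.
3. Adjust the primary comparison for characteristics fixed before pregnancy, such as age, parity, education and housing. Add one prespecified sensitivity analysis in women already in antenatal care at a single calendar date applied to both arms. A common date is needed because SC clinics have no start of AC supervision of their own; it should be no later than that start, so that AC could not yet have influenced attendance.
4. State the individual-level conclusion for clinic-attending pregnant women.

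Clinic data should not be presented as a denominator that reveals non-attendance, because clinic records contain only attenders. Showing non-attendance would take a count of pregnant women made independently of the clinics and the CHWs, which is a larger undertaking and is not needed for the changes above.

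The cost is two items at enrolment, the pre-pregnancy covariates where not already collected, a short table by arm and one extra analysis. The early-attender subset will be smaller and its estimate less precise, adjustment removes only differences in measured characteristics, and the stated population becomes narrower.

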#### AC

The CHWs in the AC will receive the initial Philani training as described above. In addition, the CHWs’ implementation will be consistently monitored and an accountability system will be established. In AC, supervisors will randomly observe home visits once every 2 weeks. CHWs in the AC will log their home visits on their mobile phones, including a rating of the content and skills addressed on the visit, children’s height and weight, and report on achievement of outcomes such as receiving the child grant, immunizations, breastfeeding, and retention and adherence to HIV care. The supervisors have two types of information, (1) personal observations of the CHW as they accompany the CHWs on their visits for 1 day every 2 weeks; and (2) reviewing data from a console as well as a folder which summarizes and documents every home visit made daily, the length of the visit, its location, the topics covered, the skills used by the CHW, and the perceived impact. The console reports also include the weight and length ratings of the child visited plotted on a growth chart. The supervisors do not change this information collected by the CHW on mobile phones, but merely review and use it for supervision and management of the CHWs. Supervision will facilitate CHW skill improvement over time. CHWs will be able to call mothers to check on illnesses such as diarrhea, provide reminders for immunizations and follow-up medical visits for HIV ARV or CD4 counts, as well as to make supportive calls to encourage depressed mothers to engage in pleasant events and a range of other motivating activities. Support, reminders, and monitoring will be the three primary functions that the supervisors will be encouraged to perform. Supervisors will not provide specific scripts or text messages for the CHWs. At each visit, the CHW enters a child’s weight and height in the mobile phone, which is translated into a WHO growth chart that both the mother and the CHW can review. The growth chart is brightly colored, clear, with a yellow color when the baby is in the desirable height-weight zone.

There will be a “flag system” to prompt the CHW and supervisor when visits are due by the CHW and when a follow-up is needed. In addition to gathering real-time data on the health of the household, the mobile phone monitoring system automatically lists all follow-up visits needed for each week. For example, the CHW is expected to reach all households in their catchment area within a maximum of a 6-month period. Pregnant mothers are to be visited monthly and every 2 weeks within the last 6 weeks of pregnancy. A household with a severely malnourished or stunted child must be visited weekly. A household with a child within one SD of the normal height and weight only needs to be visited monthly. MLHs must be visited more often both in pregnancy and post-birth, especially if there has been no reengagement in care following childbirth (See Table 2).

**Table 2 Tab2:** Identification of responsibility for administrative and implementation functions with community health workers (CHWs)

	Standard Care	Accountable Care
Hiring	Local government	Local government
Salary	Local government	Local government
Training	Initial Philani Intervention Model (PIM) training	Initial PIM training and mobile phones provided
Visit documentation	Log sheet	CHW will log home visits in real time on mobile phones and enter information about the pregnant women in a folder for follow up purposes
Supervision	Local government	PIM
Type of supervision	Log sheet	Random supervision visits every 2 weeks including real-time and data-informed feedback; support and reminders will be sent to CHW and supervisors via mobile phones (“flag system”)

